## Abstract

**Background:**

Anxiety disorders are the most common mental disorders in community settings, and they are associated with significant psychological distress, functional and social impairment. While cognitive behaviour therapy (CBT) is the most consistently efficacious psychological treatment for anxiety disorders, barriers preclude widespread implementation of CBT in primary care. Transdiagnostic group CBT (tCBT) focuses on cognitive and behavioural processes and intervention strategies common to different anxiety disorders, and could be a promising alternative to conventional CBT. This study aims to examine the effectiveness of a transdiagnostic group CBT for anxiety disorders program as a complement to treatment-as-usual (TAU) in primary mental health care.

**Methods/Design:**

The trial is a multicentre pragmatic randomized controlled trial with a pre-treatment, post-treatment, and follow-up at 4, 8 and 12-months design. ***Treatment and control groups****.* a) tCBT (12 weekly 2-h group sessions following a manualized treatment protocol); b) TAU for anxiety disorders. Inclusion criteria comprise meeting DSM-5 criteria for primary Panic Disorder, Agoraphobia, Social Anxiety Disorder and/or Generalized Anxiety Disorder. Patients are recruited in three regions in the province of Quebec, Canada. The primary outcome measures are the self-reported Beck Anxiety Inventory and the clinician-administered Anxiety and Related Disorders Interview Schedule for DSM-5 (ADIS-5); secondary outcome measures include treatment responder status based on the ADIS-5, and self-reported instruments for specific anxiety and depression symptoms, quality of life, functioning, and service utilisation. ***Statistical analysis:*** Intention-to-treat analysis. A mixed effects regression model will be used to account for between- and within-subject variations in the analysis of the longitudinal effects of the intervention.

**Discussion:**

This rigorous evaluation of tCBT in the real world will provide invaluable information to decision makers, health care managers, clinicians and patients regarding the effectiveness of the intervention. Widespread implementation of tCBT protocols in primary care could lead to better effectiveness, efficiency, access and equity for the large number of patients suffering from anxiety disorders that are currently not obtaining evidence-based psychotherapy.

**Trial registration:**

ClinicalTrials.gov: NCT02811458.

## Background

### Background and rationale

Anxiety disorders are the most common class of mental disorders [1], with a past-year estimate prevalence of 11.6% [2]. They are characterized by excessive fear, anxiety and avoidance behaviour, often develop during youth and adolescence, and are frequently chronic in the absence of treatment [3]. Over half of cases are comorbid with other anxiety and depressive disorders [4–6], and comorbidity with other mental disorders [7] and chronic physical conditions is also common [8]. Considering that they are highly prevalent, disabling, comorbid, and with an early age of onset, anxiety disorders are accountable for an extensive personal, social and economic burden for the population [9–11]. Anxiety disorders are the sixth leading cause of years of life lived with disability [12]. The scaling-up of treatment for anxiety disorders could lead to substantial health benefits and economic return on investment [13]. As global health policies are increasingly oriented towards improving public mental health [14, 15], the strengthening of primary mental health care has mobilized attention as an approach to reduce the treatment gap for mental disorders. Primary care is generally the principal point of access to care for patients with mental disorders [16], and community-based mental health interventions could play a significant role in the improvement of the quality of care for anxiety disorders from a population health perspective.

Low rates of treatment adequacy have been found for anxiety disorders in studies conducted in various countries and clinical settings [16–22]. While both pharmacological and psychological treatments are recommended for anxiety disorders in clinical practice guidelines [23, 24], and most patients report a preference for psychotherapy [25], patients are increasingly treated with antidepressant medication [26]. A key issue in the treatment gap for anxiety disorders is access to evidence-based psychological interventions [22]. Cognitive Behaviour Therapy (CBT) is the most empirically supported psychotherapy for the treatment of anxiety disorders [27–29]. Among barriers to dissemination and uptake of CBT in routine care, psychologists and psychotherapists are scarce resources in primary care settings, with varying levels of training in evidence-based treatments [30]. In that context, providing access to a high-intensity individual psychotherapy with a therapist competent in CBT for specific anxiety disorders presents numerous challenges in community-based mental health care services. CBT can be delivered in various settings and formats [31–33], and treatment approaches that have a good potential for dissemination to clinicians and implementation in community settings are thus required to improve access to mental health care [34, 35].

Transdiagnostic CBT (tCBT) is a promising intervention to improve access to evidence-based psychological treatments for patients with anxiety disorders [34, 36–38]. By relating to a conceptualization of a general syndrome underlying the psychopathology of emotional disorders [37, 39, 40], tCBT offers an alternative to diagnosis-specific protocols by proposing evidence-based therapeutic procedures for a whole class of disorders, such as anxiety disorders [34, 41–43]**.** tCBT focuses on cognitive and behavioural processes that are shared among many disorders, as well as on common intervention strategies employed across the anxiety disorders (e.g., cognitive therapy, graduated exposure). tCBT encompasses an overarching transdiagnostic treatment protocol rather than multiple evidence-based psychological treatment protocols that target specific anxiety disorders, which could facilitate training and supervision of psychotherapists [34, 35]. tCBT could also be beneficial for patients who present a complex clinical profile as it allows simultaneous treatment of several comorbid pathologies for a given client rather than sequentially addressing multiple diagnoses with different treatments [44, 45]. A number of studies support the efficacy of individual, group and computerized tCBT for anxiety disorders [46–48]. From a primary mental health care standpoint, tCBT interventions in a group modality could be particularly valuable for the dissemination of CBT. Group tCBT for mixed-diagnosis anxiety disorders facilitates treatment planning and delivery, consequently allowing the clinicians to treat more patients per workday and reduce waitlist times in the context of limited resources and expertise [34]. tCBT group protocols relevant for multiple anxiety disorders have been developed by a number of research groups, and are generally associated with large effect sizes post-treatment [34, 47]. The tCBT group intervention for anxiety disorders developed by [name] [49] has demonstrated its efficacy through a number of trials conducted in a specialized university-based anxiety disorders research clinic [45, 50, 51].

Empirical data underscore the efficacy and feasibility of tCBT group approaches, which seem to be easily adaptable to the constraints of clinical settings and offer a promising solution to the challenges of comorbidity. Group tCBT should now be assessed in community-based primary mental health care, as transferability of the intervention from a specialized anxiety disorders clinic to community settings could contribute to improved access to evidence-based psychotherapy. In the context of the public mental health organization in the province of Quebec (Canada), community-based primary mental health care teams have been implemented in each administrative region since 2005 [52]. It is in their mandate to work in collaboration with family physicians to ensure access and continuity of care for their population, and they act as a gateway to specialized care. Clinical teams typically comprise psychologists, psychoeducators, social workers and nurses, and they are actively developing group treatments to meet high volume needs of the population for psychotherapy and manage their waiting lists, which is a good indicator of the feasibility and acceptability of group interventions for large-scale implementation.

In the present study, we aim to examine the effectiveness of group tCBT in the real world as it shows great potential to improve health outcomes for individuals with anxiety disorders. In the perspective of a pragmatic trial to examine the effectiveness of the intervention in terms of generalizability, feasibility and cost/effectiveness, we propose a comparative clinical effectiveness trial of group tCBT for anxiety disorders delivered in the primary care setting as a complement to usual care. Secondary objectives also encompass an economic evaluation as well as an embedded qualitative study to provide information to stakeholders on implementation issues.

### Objectives

The aim of the trial is to examine the effectiveness of group tCBT, as a complement to treatment-as-usual (TAU) in primary care, to reduce anxiety symptoms of adults with Panic Disorder, Agoraphobia, Social Anxiety Disorder and/or Generalized Anxiety Disorder compared to TAU. *Primary question*: When a group tCBT is added to TAU in primary care for a mixed group of patients with Panic Disorder, Agoraphobia, Social Anxiety Disorder and/or Generalized Anxiety Disorder, is it more effective to reduce anxiety symptoms than TAU alone? *Hypothesis*: Group tCBT will be more effective than TAU alone, showing the superiority of the tCBT intervention with usual care alone.

#### Secondary questions

a) Considering clinically significant outcomes for patients with anxiety disorders, is there a significant difference between groups in terms of remission rates and high-end functioning rates based on a clinician-rated measure? b) Is there a significant difference between groups on functioning and quality of life? c) Is there a differential treatment effect size based on diagnostic-specific measures for subgroups of patients meeting DSM-5 criteria for specific anxiety disorders at baseline? d) Is there maintenance of gains at follow up? e) Does the severity of depressive symptoms at baseline moderate treatment effectiveness for the primary outcome measures? f) Does the presence of an antidepressant and/or benzodiazepine medication at baseline moderate treatment effectiveness for the primary outcome measures? g) Is there differential treatment effectiveness based on the principal anxiety disorder at baseline? h) Is there a differential compliance rate and treatment effect size based on gender? i) Is tCBT as a complement to TAU preferable to TAU only based on a cost-effectiveness and cost-utility analysis (i.e., economic evaluation, not described in the protocol)? j) What are the acceptability and feasibility of the tCBT intervention for patients and therapists (i.e., embedded qualitative study, not described in the protocol)?

### Trial design

The trial is an investigator-initiated study designed as a two-arm parallel group multicentre pragmatic superiority RCT, with a 1:1 allocation at the level of the individual. The proposed trial conforms to the SPIRIT guidance for protocols of clinical trials [53].

## Methods

### Participants, interventions and outcomes

#### Study setting

The trial is being conducted in three health and social service administrative regions in the province of Québec, Canada. The network organization in Québec comprises regional integrated health and social services centres accountable for the delivery of care and services within a population responsibility framework. The universal health insurance system provides health care and social services coverage for the population. However, the organisation and delivery of mental health care varies considerably within each administrative region, and the same variability also applies to complementary mental health services available in the private sector (e.g., psychologists in private practice). We purposefully selected the following three study sites based on diversity (e.g., population size, region, university teaching hospital, psychiatric hospital, primary care mental health services, primary care network). The integrated health and social services centre for Quebec City and adjacent areas (i.e. *CIUSSS de la Capitale-Nationale)* serves an urban and rural population of 737,000 inhabitants over a large territory of 18,600 KM^2^; the study site is in the Quebec City region (89% of the territory population). The health and social services centre for the region of Laval (i.e. *CISSS de Laval*) serves a predominantly urban population of 435,000 inhabitants and is part of the Greater Montreal metropolitan area (over four million inhabitants). The health and social services centre for the Estrie region (i.e. *CIUSSS de l’Estrie - Centre Hospitalier universitaire de Sherbrooke)* serves a population of 474,000 inhabitants over a large territory of 13,000 km^2^; the study site is in Sherbrooke (> 164,000 inhabitants). All selected sites agreed to provide in-kind support for the study, including: 1- public sector psychologists and psychotherapists participation as co-therapists in treatment groups; 2- office space in primary care settings for participant’s assessment and treatment delivery. The institutional review boards at each site approved the protocol.

#### Eligibility criteria

In a pragmatic approach to eligibility and patient recruitment, the clinical trial is being conducted with a community sample of patients with anxiety disorders. Based on current knowledge about heterogeneous clinical profiles of patients with anxiety disorders in the primary care setting [22], eligibility criteria are as broad as feasible in terms of anxiety severity, psychiatric comorbidity, diagnosis status and ongoing treatments to reflect real life primary care patients. We include participants meeting the following inclusion criteria: (1) aged 18 to 65; (2) fluent in spoken and written French; (3) meeting DSM-5 diagnostic criteria for at least one of the following anxiety disorders as a primary mental disorder: Panic Disorder, Agoraphobia, Generalized Anxiety Disorder and/or Social Anxiety Disorder according to a clinical severity rating ≥ 4 for the Anxiety Disorders Interview Schedule for DSM-5 (ADIS-5) [54]. We exclude patients meeting the following exclusion criteria: (1) active suicidal intentions, psychosis, bipolar disorder, and active substance-related and addictive disorder in the past 12 months; (2) marked cognitive impairment [55]; (3) consultation with a psychiatrist in the past 12 months. These exclusion criteria were selected on the basis that it is unlikely that patients with this clinical profile would fully benefit from the group, and that patients accessing specialized mental health care would not be typical cases for primary care tCBT group treatment. Co-occurring mild to moderate psychiatric disorders, including major depression, obsessive-compulsive disorder or posttraumatic stress disorder, are permitted.

#### Interventions

##### Group tCBT for anxiety disorders plus treatment-as-usual (TAU)

The experimental condition is the transdiagnostic group cognitive-behaviour therapy (tCBT) program published by [name] (2012) [49]. The tCBT intervention encompasses four components: 1- *Education and self-monitoring:* education on the nature of anxiety and its treatment, and introduction to self-monitoring of triggers and responses to anxiety-provoking stimuli; 2- *Specific cognitive restructuring:* thinking errors and automatic thoughts associated with anxiety; 3- *Graduated exposure and response prevention:* gradual confrontation of fear-provoking stimuli; 4- *Generalized cognitive restructuring:* examining core beliefs and perceptions of everyday life. Table 1 presents the outline of the protocol. A written treatment protocol guides the delivery of the groups for the therapists. Patients receive a tCBT workbook at the first treatment session. The tCBT group includes weekly 2-h sessions with 8–10 patients during a 12-week period. A brief telephone or face-to-face individual preliminary contact is established with each participant by one of the co-therapists during the 2 weeks prior to the first session of tCBT to introduce the treatment and build an exposure hierarchy.

**Table 1 Tab1:** tCBT treatment components

Components	Strategies
Psychoeducation (1.5 sessions)	Components of anxiety
	Treatment rationale
	Causes of anxiety
	Daily self-monitoring
Cognitive Restructuring (1.5 sessions)	Identify anxiety thoughts
	Identify misinterpretations and misappraisals
	Challenge and develop balanced interpretation or appraisal
Exposure (6 sessions)	Develop Fear Hierarchy
	Conduct in-session and homework exposure while engaging in response prevention
Schema-Based Cognitive Restructuring (2 sessions)	Identical to previous Cognitive Restructuring, but emphasis on general neurotic style
	The “tendency to interpret neutral or ambiguous stimuli as negative, threatening, and personally relevant”
Termination/Relapse Prevention (1 session)	Continued self-exposure and cognitive restructuring
	Lapses vs. relapses
	Emergency Action Plans

Groups are being delivered by two psychologists or psychotherapists accredited by the provincial regulatory body for the practice of psychotherapy. Primary therapists are PhD level private practice psychologists with a CBT approach and at least 2 years of clinical experience to ensure basic CBT competence for treatment fidelity. In a pragmatic perspective on treatment delivery, the co-therapists are selected by the health care managers at each study site (in-kind contribution) to reflect the range of clinical backgrounds of therapists working in the public sector in Québec. The training of co-therapists also supports capacity building and mentorship in tCBT in public sector mental health care services. Therapists’ training was initially provided during a centralized two-day workshop with the tCBT protocol developer ([name]), and followed by ongoing supervision by investigators ([name], PG). In the event of the need to recruit more therapists after the initial training session, tailored individual training are provided to therapists ([name]). Supervision ([name], PG) is provided to co-therapists at predefined times during the delivery of the intervention (pre-treatment, between sessions 3 and 4, between sessions 6 and 7, between sessions 10 and 11, post-treatment), as well as as-needed. Fidelity to the tCBT program is monitored through the recording of all treatment sessions. Therapeutic treatment adherence and competence is assessed by a random review of 30% of audio recordings during all sessions with a 5-point treatment integrity rating scale developed by the author of the intervention ([name]) [56] and used in previous trials [51, 57, 58]. Patient compliance is supported through high-quality interventions (e.g., trained and experienced therapists, supervision, monitoring treatment adherence and competence) and the provision of group interventions in a primary care setting (e.g., access, reduced mental health stigma) at convenient times (including evenings).

##### Treatment-as-usual

The TAU control group continues receiving usual care as a comparator. For this pragmatic clinical trial, no restrictions are imposed upon participation regarding having a family physician or treatment of mental disorders, as we are interested in comparing the added value of tCBT in real world conditions. Service utilization is being documented at each assessment period throughout the trial. As in other pragmatic trials, it should be noted that participation in the study may be associated with uncontrolled variations in mental health care seeking among patients for several reasons (e.g., instilling hope and motivation; awareness through comprehensive mental health assessment; knowledge about CBT; waiting for delayed intervention in the control group).

#### Participant assessment

A description of patient assessment timeline is presented in Table 2. They comprise instruments with good psychometric properties, and previously used in transdiagnostic and diagnostic-specific interventions for anxiety disorders to facilitate comparability [34, 59].

**Table 2 Tab2:** Study schedule of patient assessment

Timepoint	Enrolment	Intervention	Follow-up			
	-T_1_		T_1_	T_2_	T_3_	T_4_
Clinician-administered measures						
Anxiety and Related Disorders Interview Schedule for DSM-5 (ADIS-5)	X		X		X	
Sociodemographic variables	X		X	X	X	X
Service utilization and medication	X		X	X	X	X
World Health Organization Health and Work Performance Questionnaire	X		X	X	X	X
Self-administered booklet						
Beck Anxiety Inventory	X		X	X	X	X
Social Phobia Inventory	X		X	X	X	X
Penn State Worry Questionnaire	X		X	X	X	X
Panic Disorder Severity Scale	X		X	X	X	X
Mobility Inventory for Agoraphobia	X		X	X	X	X
Patient Health Questionnaire	X		X	X	X	X
Insomnia Severity Index	X		X	X	X	X
Sheehan Disability Scale	X		X	X	X	X
EuroQol (ED-5D)	X		X	X	X	X
CDC Healthy Days Measures	X		X	X	X	X
Disease Burden Morbidity Assessment	X		X	X	X	X
Mental Health Self-Management Questionnaire	X		X	X	X	X
Mental Health Continuum –Short Form	X		X	X	X	X
MOS Social Support Survey	X		X	X	X	X
Completed during therapy (tCBT GROUP)						
Anxiety Disorder Diagnostic Questionnaire - weekly		X				
Credibility/Expectancy Questionnaire		X				
Working Alliance Inventory		X				
Gross Cohesion Scale		X				

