##### Diagnostic interview

The **Anxiety and Related Disorders Interview Schedule for DSM-5** (ADIS-5) [54] is a semistructured interview designed to assess DSM-5 diagnostic criteria for anxiety disorders and comorbid mental disorders (e.g., mood disorders, substance use). The interviewer determines the presence of symptoms and rates their clinical severity (CSR) on a scale from 0 (no symptoms) to 8 (extremely severe symptoms) with increasing values indicating increased distress/interference, and a clinical threshold of 4 or higher. The ADIS-5 is initially used to assess eligibility criteria for the study. Co-occurring mild to moderate major depression, obsessive-compulsive disorder or posttraumatic stress disorder are permitted at the following conditions: a) CSR of 6 or lower; b) CSR at least one-point lower than for the principal anxiety disorder. The ADIS-5 will also be used to examine treatment outcomes through the dimensional CSR scales for each mental disorder. The clinician-rated measure of outcomes will be based on the CSR of the ADIS-5 [54] for the principal anxiety disorder. While there are no data on the psychometric properties of the ADIS-5, the ADIS-IV was shown to have good interrater reliability when assessing the presence of mental disorders [4]. Interrater reliability will be assessed for 25% of audio-recorded ADIS-5 diagnostic interviews at each assessment period by randomly selected clinical evaluators.

The initial interview also comprises a clinician-administered questionnaire on sociodemographic data, and a brief structured interview on health care costs used in previous studies [32] to obtain information on mental health consultations (e.g., type of professional, duration, costs), psychotropic medication (name, dosage, length of time), indirect costs (e.g., absenteeism) and other related variables such as previous therapy experience and treatment preference. The questionnaire also examines work performance based on the short version of the **World Health Organization Health and Work Performance Questionnaire** (HPQ) [60].

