#### Blinding

Blinding of trial participants and therapists is not possible in this trial. Concealment of the treatment allocation is maintained for the clinical evaluators, research team and data analyst, with the exception of the research coordinator. Participants are asked not to discuss group participation with clinical evaluators. The randomization sequence will not be broken in the data set, with random codes (“A” and “B”), until the analyses for the primary outcomes are completed. The sequence for a specific participant will be broken in case of an incident if requested by the independent Data Safety and Monitoring Committee (DSMC).

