### Data collection, management, and analysis

The clinical assessment of participants is conducted in person (T_0_, T_1_, T_3_) by trained PhD level evaluators at the three sites or by telephone (T_2_ and T_4_; interview on health care costs) by the research coordinator (AB). The evaluators received a one-day training on the ADIS-5 as well as additional training to ensure optimal data collection (e.g., missing data, patient retention). Regular supervision ([name], PG) is provided to clinical evaluators throughout the duration of the data collection, particularly regarding the ADIS-5 assessments. For the post-treatment and follow-up assessments, participants also receive a letter by mail reminding them of the upcoming clinical evaluation, including a booklet with a stamped envelope. The research coordinator manages contacts with participants for scheduling assessments.

A procedure is followed to promote participant retention and complete follow-up. Treatment and follow-up are managed as different functions by different research team members, with the data collection schedule independent of treatment status and adherence to protocol. The T_2_ telephone assessment of participants contributes to avoid recall bias for service utilization as well as maintain patient’s interest in the study by regular contact with research personnel in between face-to-face assessment periods. In particular cases of participants from either groups non-compliant with follow-up assessment periods, we try to minimize the assessment burden by having them complete only the BAI primary outcome rather than the full evaluation.

Data entry, coding, storage and analysis is managed (PR) at Université de Sherbrooke on a secure server with systematic backups. Double data entry is being conducted for 10% of patient questionnaires throughout the trial to promote data quality, and data entry is under the responsibility of a trained research assistant.

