#### Control for bias sources

The primary means to avoid bias include the randomization scheme; the masked data collection by clinical evaluators who enrol and evaluate participants throughout the project while being uninformed of treatment assignment (with an incident report and reassignment procedure if they become unmasked); the masked research hypotheses for participants.

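### At T1 and T3 the masked CSR raters appear also to take the mental-health service-use history, which creates a foreseeable risk of unmasking the only masked primary outcome

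*Protocol article*

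**What the plan says.** - **Schedule.** Under the clinician-administered heading of Table 2 (Participant assessment), the ADIS-5 row reads "Anxiety and Related Disorders Interview Schedule for DSM-5 (ADIS-5) X X X", that is enrolment, T1 and T3. In the same block the service-use row reads "Service utilization and medication X X X X X", that is enrolment and T1 to T4. The Treatment-as-usual section agrees: "Service utilization is being documented at each assessment period throughout the trial".
- **Who does it.** The data collection section states: "The clinical assessment of participants is conducted in person (T_0_, T_1_, T_3_) by trained PhD level evaluators". It assigns the research coordinator only the T2 and T4 telephone interviews on health care costs.
- **What is asked.** The Diagnostic interview section describes, for the initial interview, a brief structured interview "to obtain information on mental health consultations (e.g., type of professional, duration, costs), psychotropic medication (name, dosage, length of time").
- **Masking.** The Blinding section conceals allocation from evaluators, research team and data analyst, with the coordinator as the exception. It adds: "Participants are asked not to discuss group participation with clinical evaluators". The section on control of bias counts among its primary means "the masked data collection by clinical evaluators who enrol and evaluate participants throughout the project while being uninformed of treatment assignment". Should an evaluator become unmasked, that section provides for an incident report and reassignment.
- **Outcomes that depend on it.** The CSR of the principal anxiety disorder is one of two primary outcomes. The other, the BAI, is self-reported. High end-state functioning (CSR of 2 or lower) and responder status (CSR below 4) are derived from the CSR.

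**The concern.** At T1 a tCBT participant has been offered twelve weekly 2-hour group sessions led by psychologists or psychotherapists. A structured question about recent mental health consultations, with type of professional and duration, invites that participant to describe them. The participant has also been asked not to mention the group. Unless study sessions are excluded from the question, the two instructions pull in opposite directions: a full answer may unmask the rater, and a guarded one leaves the service-use record incomplete.

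The stakes lie with the CSR. Participants cannot be masked, so the self-reported BAI has no such protection. The CSR is the only primary outcome that masking guards, and both ADIS-5 secondary outcomes inherit whatever bias enters it.

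**Working it through.** **1. Are the two tasks at the same visit?** Yes. Table 2 marks both the ADIS-5 and service use at T1 and T3, in the same clinician-administered block.

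**2. Does the same person do both?** This is explicit only for T0, where the Participant timeline has one trained evaluator administer the ADIS-5 and the questionnaire on health care costs. For T1 and T3 it is the natural reading: the evaluators run the in-person visits, the coordinator is named only for T2 and T4, and the timeline marks T2 and T4 as service use only, which implies that the in-person visits cover service use and more. No sentence assigns the T1 and T3 service-use items to anyone else.

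**3. Would the answer be informative about the arm?** Often, but not always. The content is described for the initial interview, and Table 2 then repeats the item at each later time point. TAU participants may also see psychologists, because usual care is unrestricted. However, the randomization section says that specific CBT for anxiety disorders is rarely available in primary care in this setting, so a report of recent weekly group sessions would shift a rater's belief.

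**4. Do the stated safeguards close the gap?** The request for silence conflicts with the question, and reassignment operates only after unmasking has occurred. The text does not say that the CSR is rated first, that study sessions are excluded, or that the tasks are divided.

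**5. Illustration of size.** The Sample size section gives d = 0.45, two-sided alpha 0.03, 80% power and 15% loss. The two-sample noncentral t calculation returns 182 in total (91 per arm, power 0.801), and 182 / 0.85 = 214.1, rounded up to 215. Both of the plan's figures reproduce, and neither changes under this point.

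The document gives no size for rater bias, so b below is an assumption: the average between-arm shift in CSR rating, in SD units, favouring tCBT, with no true effect. By the normal approximation:

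P(significant in favour of tCBT) = 1 − Φ(2.170 − b × √(91/2)), with √(91/2) = 6.745

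| b (SD) | b × 6.745 | 2.170 minus that | Probability |
|---|---|---|---|
| 0 | 0 | 2.170 | 1.5% |
| 0.05 | 0.337 | 1.833 | 3.3% |
| 0.10 | 0.675 | 1.495 | 6.7% |
| 0.15 | 1.012 | 1.158 | 12.3% |
| 0.20 | 1.349 | 0.821 | 20.6% |
| 0.30 | 2.024 | 0.146 | 44.2% |

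If only some ratings are affected, b shrinks in proportion. With half the tCBT ratings affected, shifts of 0.10, 0.20 and 0.30 SD in those ratings average 0.05, 0.10 and 0.15 SD, giving 3.3%, 6.7% and 12.3%.

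**The case against.** A reader might infer that the interview itself discloses the arm in every patient, so that the trial is left with no masked efficacy measure. The document does not support that, for these reasons:

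- The consultation content is described for the pre-randomization interview. The wording used at T1 and T3 is not given.
- Nothing says that trial sessions are elicited. Therapists already record each participant's presence after every session, so the trial does not need participants to report them.
- Seeing a psychologist does not identify the arm. Usual care is unrestricted, private psychologists are available, and the plan expects care-seeking to vary.
- The ADIS-5 is listed ahead of the service-use items in both Table 2 and the timeline. If that is the order of the visit, the T1 symptom interview comes first. Carry-over to T3 needs the same evaluator to return, which is not stated.
- Question wording and visit order may sit in the full protocol or an assessment manual that the article condenses.
- The bias sizes have no source in the document.

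All of this stands against the stronger reading. It does not remove the point. The article fixes a schedule that, followed as written, puts an arm-informative question to the masked rater, and the safeguards it chooses to describe do not prevent the exposure. A listing order in a table is not a rule that the rating is closed before the question is asked.

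**Conclusion.** The point holds as a foreseeable risk of unmasking the clinician-rated co-primary outcome and the two measures derived from it. It is not a demonstration that masking fails. It rests on two inferences: that the evaluators take service use at T1 and T3 as well as at T0, and that the consultation questions at those visits resemble those at baseline. Both are the natural reading, and neither is explicit for those visits. The BAI is unaffected by this route.

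The size is unknown. The false-positive figures show only that the CSR comparison is sensitive to modest bias: an average shift of 0.20 SD is 44% of the design effect (0.20 / 0.45) and would raise the chance of a false result favouring tCBT from 1.5% to about 21%. They are not an estimate of what happened in this trial.

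**What to change.** 1. At T1 and T3, have the evaluator rate and lock the CSR before any service-use question is asked.
2. Preferably, have the research coordinator, who is already unmasked, collect the consultation items by telephone at T1 and T3 as at T2 and T4. This takes the question away from the rater and keeps an interview format. Moving the items to the self-completed booklet would mix interview and self-report within the service-use data.
3. Exclude study-group sessions from the questions and take them from the therapists' attendance log. This reconciles the service-use interview with the request not to discuss the group.
4. Record the evaluator's guess of allocation after each rating, and report it by arm.
5. For visits already completed, report the unmasking incidents and reassignments.

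The cost is slightly more coordinator time and a small change of procedure part-way through follow-up. By the article's dates, enrolment closed in February 2018 and the last group was due to finish in May 2018. Many T1 visits may therefore be past, and steps 1 to 4 would protect only the remaining T1 and T3 visits. If the full protocol already orders or separates the tasks, a sentence saying so is enough.
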